## Abstract

**Background:**

Experiencing a critical illness may be a stressful life event that is also associated with cognitive dysfunction during and after the intensive care unit (ICU) stay. A deep-tech solution based on non-immersive virtual reality, gamification and motion capture called Rehabilitation Gaming System for Intensive Care Units (RGS-ICU) has been developed that includes both cognitive stimulation and relaxation protocols specifically designed for patients with critical illness. This study aims to evaluate whether the cognitive and relaxation protocols of the RGS-ICU platform are 1) effective in improving neuropsychological outcomes during and after ICU stay and 2) safe for patients with critical illness.

**Methods:**

This is a study protocol for a multicenter longitudinal randomized clinical trial. At least 80 patients with critical illness will be included: 40 experimental subjects and 40 control subjects. Patients in the experimental group will receive daily 20-min sessions of cognitive stimulation and relaxation with the RGS-ICU platform adjuvant to standard ICU care in their own rooms during the ICU stay and until discharge from the ICU or up to a maximum of 28 days after randomization, provided they are alert and calm. Patients in the experimental group will be constantly monitored as part of standard ICU care to ensure the safety of the intervention and that no avoidable adverse events occur. Patients in the control group will receive standard ICU care. The primary outcome is objective cognition 12 months after ICU discharge, assessed with a composite index including measures of attention, working memory, learning/memory, executive function and processing speed. The secondary outcome is the safety of the intervention, assessed by considering the number of sessions terminated early due to unsafe events in physiological parameters. Other outcomes are comfort experienced during the ICU stay, and subjective cognition, mental health (anxiety, depression and post-traumatic stress disorder), functionality and health-related quality of life 12 months after ICU discharge.

**Discussion:**

The expected results are 1) better neuropsychological outcomes during and after the ICU stay in patients in the experimental group compared to patients in the control group and 2) that the cognitive and relaxation protocols of the RGS-ICU platform are safe for patients with critical illness.

**Trial registration:**

Clinicaltrials.gov NCT06267911. Registered on February 20, 2024.

**Supplementary Information:**

The online version contains supplementary material available at 10.1186/s12888-024-06360-4.

## Introduction

### Background and rationale

Admission to an intensive care unit (ICU) is a potentially traumatic experience, especially for patients who are mentally vulnerable. Beyond the stress and anxiety associated with the ICU environment and medical procedures, survivors of critical illness are at risk of developing cognitive and psychological sequelae related to post-intensive care syndrome (PICS) [1, 2]. These sequelae can persist for months or even years after ICU discharge, compromise patients’ functionality and health-related quality of life (HRQoL) [3, 4], and carry high personal, social, medical and economic costs [5].

Cognitive deficits related to PICS, whether objective or subjective, typically affect attention, working memory, learning/memory, executive function and processing speed [6, 7]. Psychological disturbances often include anxiety, depression and post-traumatic stress disorder (PTSD) as the most common mental health manifestations [8, 9]. The main risk factors associated with these sequelae are delirium, invasive mechanical ventilation (MV) and prolonged deep sedation during ICU stay [10–12]. In contrast, cognitive reserve (i.e., the patient's brain's resistance to neurological damage) may be a protective factor [6, 7, 13, 14].

During the ICU stay, patients with critical illness spend most of the day bedridden, may have verbal communication problems and develop ICU-acquired muscle weakness [15]. To date, several e-health solutions have been proposed to cognitively stimulate and help relax these patients, but few studies have examined whether these types of interventions are effective in improving neuropsychological outcomes during and after the ICU stay and safe for patients with critical illness [16–18].

One such e-health solution is the Early Neurocognitive Rehabilitation in Intensive Care (ENRIC) platform. To the authors’ knowledge, this was the first non-immersive virtual reality (VR)-based cognitive intervention designed and developed specifically for patients with critical illness and the ICU environment (Clinicaltrials.gov Identifier: NCT02078206). In a first proof-of-concept (PoC) study (*n* = 20), Turon et al. [19] demonstrated the feasibility, safety, tolerability and potential efficacy of this intervention to stimulate the brain during ICU stay using a surrogate measure of cognitive function (i.e., heart rate variability, HRV). In a second randomized clinical pilot (*n* = 42, 21 experimental subjects and 21 control subjects), Navarra-Ventura et al. [13] demonstrated that cognitive stimulation with the ENRIC platform improved working memory performance shortly after ICU discharge and that this advantage was maintained in the long term, in line with results previously obtained using HRV. A trend toward reduced rates of anxiety and depression was also observed, although it did not reach statistical significance. However, this study was limited by an intervention that included only cognitive protocols but no specific relaxation content and by the high dropout rate related to the Covid-19 pandemic situation, with only 10 experimental subjects and 14 control subjects completing all post-ICU follow-up visits. Interestingly, in another PoC and pilot study (*n* = 20), Martí-Hereu et al. [20] demonstrated that watching videos of relaxing experiences using immersive VR goggles is feasible, tolerable and can help reduce anxiety during ICU stay in patients with critical illness.

Based on these and other experiences in stroke neurorehabilitation [21], a specific solution for patients with critical illness called Rehabilitation Gaming System for Intensive Care Units (RGS-ICU) was designed and developed that includes both cognitive stimulation protocols modeled after the ENRIC platform exercises and relaxing videos set in nature and fantasy landscapes to promote stress and anxiety reduction in patients with critical illness.

The following is the study protocol of a randomized clinical trial (RCT) using the RGS-ICU platform whose overall objective is to evaluate the efficacy and safety of cognitive stimulation and relaxation as an adjunct to standard ICU care (experimental condition) compared to standard ICU care alone (control condition).

### Objectives and hypotheses

The main objective is to assess whether patients in the intervention group show better objective cognitive performance than patients in the control group three and 12 months after ICU discharge. The secondary objective is to assess whether the cognitive and relaxation protocols of the RGS-ICU platform are safe for patients with critical illness. Other objectives are to explore whether patients in the intervention group show greater comfort during the ICU stay, as well as better outcomes in subjective cognition, mental health (anxiety, depression and PTSD), functionality and HRQoL than patients in the control group three and 12 months after ICU discharge.

The main hypothesis is that patients in the intervention group will show better objective cognitive performance than patients in the control group three and 12 months after ICU discharge. The secondary hypothesis is that the cognitive and relaxation protocols of the RGS-ICU platform will be safe for patients with critical illness. Other hypotheses are that patients in the intervention group will show greater comfort during the ICU stay, as well as better outcomes in subjective cognition, mental health (anxiety, depression and PTSD), functionality and HRQoL than patients in the control group three and 12 months after ICU discharge.

### Trial design

A two-arm, parallel group, open-label, superiority RCT with a 1:1 allocation ratio has been designed to evaluate the efficacy and safety of receiving cognitive stimulation and relaxation as an adjunct to standard ICU care (experimental [RGS-ICU] condition) compared with receiving standard ICU care alone (control [treatment as usual, TAU] condition).

## Methods

The Standard Protocol Items: Recommendations for Interventional Trials (SPIRIT) reporting guidelines have been used to write this study protocol (Additional file 1) [22].

### Study setting

Four centers are participating in this RCT: the Parc Taulí University Hospital and the Parc Taulí Research and Innovation Institute in Sabadell, Barcelona (Catalonia), and the Son Llàtzer University Hospital and the University of the Balearic Islands-Research Institute of Health Sciences in Palma, Mallorca (Balearic Islands), Spain.

The Parc Taulí and Son Llàtzer University Hospitals have a total of 57 medical-surgical ICU beds between the two centers, both in single (*n* = 50 beds) and shared (*n* = 7 beds) rooms, which admit about 1,400 patients with critical illnesses each year, of whom 300 patients are expected to be candidates for participation in the study.

### Eligibility criteria

Included will be 1) adult patients (≥ 18 years); 2) admitted to a medical-surgical ICU; 3) for respiratory failure, cardiogenic shock or septic shock; 4) with an expected ICU stay of ≥ 48 h; 5) resident in Catalonia or the Balearic Islands; 6) who speak Catalan and/or Spanish; and 7) who can give consent on their own or through an authorized representative (e.g., a family member).

Patients will be excluded if they have 1) a history of intellectual disability or other neurodevelopmental disorders, such as autism spectrum disorder or attention deficit/hyperactivity disorder; 2) a history of neurological disorder, dementia or other neurodegenerative disease, such as epilepsy, Alzheimer's disease, Parkinson's disease or multiple sclerosis; 3) a history of brain damage, such as traumatic brain injury or stroke; 4) history of severe psychiatric illness, such as psychotic, bipolar, depressive, obsessive–compulsive, post-traumatic or personality disorder; 5) suspected or confirmed substance use disorder; 6) suspected or confirmed communicable disease in an isolated patient; 7) uncorrected hearing or visual impairment; 8) any medical condition that prevents safe upper extremity mobility, such as skin lesions, burns or fractures; 9) life expectancy < 12 months; or 10) are enrolled in another RCT that does not allow co-enrollment.

### Intervention

The main objective of the intervention is to provide cognitive stimulation and relaxation specifically tailored to the needs of patients with critical illness and the characteristics of the ICU environment, fostering motivation and engagement with the sessions, regardless of the accuracy of the responses. To improve adherence, the cognitive and relaxation protocols of the RGS-ICU platform are based on non-immersive VR, gamification and motion capture to reduce monotony and boredom during sessions and avoid frustration.

#### Characteristics of the RGS-ICU platform

The RGS-ICU platform has been designed at the Parc Taulí Research and Innovation Institute with the collaboration of the University of the Balearic Islands-Research Institute of Health Sciences by a multidisciplinary team of (neuro)psychologists, psychiatrists, intensivists, nurses, and other biomedical researchers, and has been developed by a group of software engineers from Eodyne Systems S.L., a company dedicated to the development of science-based solutions for intervention, monitoring, diagnosis and prognosis in brain health. It consists of a personal computer, a flat-screen TV and an imager for motion capture placed on a medical cart for easy transfer to each ICU bed. The system captures and interprets the patient's upper extremity movements using machine vision middleware that connects these movements to multimedia content for cognitive stimulation and relaxation. This approach to patient-system interaction avoids the risk of cross-infection inherent in sharing physical devices such as touch screens or game controllers. Although patients do not have physical contact with any component of the RGS-ICU platform at any time, for infection control reasons, it can be easily cleaned and disinfected after each session (Fig. 1 and Additional file 2).

**Fig. 1 Fig1:**
[figure not shown]
Schematic diagram of the RGS-ICU platform, bedside monitor and ventilator. RGS-ICU, Rehabilitation Gaming System for Intensive Care Units

The RGS-ICU platform is switched on when plugged in to a power source. To adapt the system to the patient's upper extremity mobility capabilities, it is necessary to calibrate the motion sensor and algorithm and adjust the distance between the patient and the webcam before each session of cognitive stimulation. To do this, the patient will be asked to raise one of his or her upper extremities against gravity in front of the webcam sensor at an angle of 45 to 90 degrees to the body to calibrate motion detection and recognition. Occasionally, the patient’s ICU bed will need to be raised or lowered. Bed adjustments and calibration of the motion capture system take less than 2 min. Relaxation protocols are passive exercises in which patients do not have to move their upper extremities and therefore do not require motion sensor calibration.

The RGS-ICU platform includes seven gamified cognitive protocols with six levels of difficulty, each of them specifically designed to stimulate specific cognitive domains: attention (“Garden” and “Butterflies”), working memory (“Universe” and “Numbers”), learning/memory (“Beach” and “River”), and executive function (“Aquarium”), whereas processing speed is cross stimulated in all protocols (Fig. 2). It also includes seven videos with relaxing music and nature sounds to reduce stress and anxiety related to the ICU stay. Of these, six videos are set in natural environments, either with the camera static (“Sunrise among poppies”, “Calm at the lake” and “The swaying of the waves”) or moving from the air (“Flying over the fields”, “Relaxing on the beach” and “The sound of water”), while the seventh video is set on a fantasy island and simulates a relaxing walk (“Walk around the island”) (Fig. 3). Finally, an infographic on the ICU environment and the characteristics of the cognitive, mental and physical state of patients with critical illness is included for psychoeducational purposes.

**Fig. 2 Fig2:**
[figure not shown]
Examples of gamified cognitive protocols of the RGS-ICU platform. RGS-ICU, Rehabilitation Gaming System for Intensive Care Units

**Fig. 3 Fig3:**
[figure not shown]
Examples of relaxing protocols of the RGS-ICU platform. RGS-ICU, Rehabilitation Gaming System for Intensive Care Units

Additional file 3 is a video with four examples of the gamified cognitive protocols of the RGS-ICU platform. Additional file 4 includes usability and satisfaction data with the RGS-ICU platform from a group of 15 patients with critical illness.

#### Experimental condition: RGS-ICU group

Patients assigned to this arm will receive flexible cognitive stimulation and relaxation sessions in addition to standard ICU care every day between 9 a.m. and 1 p.m. in their own rooms if they score ≥ 13 on the Glasgow Coma Scale (GCS) [23] and between -1 and + 1 on the Richmond Agitation-Sedation Scale (RASS) [24]. Delirium (score ≥ 3 on the Confusion Assessment Method for the ICU-7, CAM-ICU-7) in cooperative patients capable of following simple commands will not preclude participation in sessions [25–27]. All sessions will be guided and supervised by trained study staff, including research (neuro)psychologists and clinical staff, when medical, nursing or room cleaning procedures are not being performed.

The type and difficulty levels of the cognitive stimulation and relaxation protocols included in each session will be determined by the patient's ability to interact with the RGS-ICU platform, assessed daily at the beginning of the session considering mental status (consciousness [GCS], sedation/alertness [RASS] and delirium [CAM-ICU-7]) and mobility level (ability to lift and hold at least one upper extremity straight against gravity). To adapt the intervention to these variables, different types of interaction and workload have been established, which are summarized in four types of patient profiles (Table 1 and Fig. 4).

**Table 1 Tab1:** Patient profile according to mental status and mobility level

Mental status			Mobility level	Patient profile
**GCS score**	**CAM-ICU-7 score**	**RASS score**		
13–15	Negative (0–2)	0	Normal^a^	Type 1^c^
			Reduced^b^	Type 2^d^
		-1 or + 1	Normal^a^	Type 3^e^
			Reduced^b^	Type 4^f^
	Positive (3–7)	-1 to + 1	Normal^a^	Type 3^e^
			Reduced^b^	Type 4^f^

*GCS* Glasgow Come Scale, *CAM-ICU-7* Confusion Assessment Method for the Intensive Care Unit-7, *RASS* Richmond Agitation-Sedation Scale

^a^Patient lifts and holds at least one upper extremity straight against gravity without difficulty

^b^Patient lifts and holds upper extremities straight against gravity with difficulty

^c^Maximum interaction and high level of cognitive demand

^d^Minimal interaction and high level of cognitive demand

^e^Moderate interaction and low level of cognitive demand

^f^Minimal interaction and low level of cognitive demand

**Fig. 4 Fig4:**
[figure not shown]
Types of patient profile according to RASS, CAM-ICU-7 and mobility level. RASS, Richmond Agitation-Sedation Scale; CAM-ICU-7, Confusion Assessment Method for the Intensive Care Unit-7. Patients with a normal level of mobility lift and hold at least one upper extremity straight against gravity without difficulty. Patients with a reduced level of mobility lift and hold the upper extremities straight against gravity with difficulty

Although the intervention may vary according to the type of patient profile, sessions have been standardized as follows: the average duration of a session will be 15–20 min, but patients will be encouraged to continue up to a maximum of 30 min if adequately tolerated. At the beginning of each session, patients will be oriented in space and time (about 1 min). Then, up to a maximum of four cognitive protocols (about 5 min each) will be applied to stimulate attention, working memory, learning/memory and/or executive function (in that order), as appropriate. By default, progression from easier to more difficult levels within a cognitive protocol will be made after successfully passing the previous level, so that patients who complete a portion of the exercises will be able to start the next session from the last level completed without errors. Preferably after cognitive stimulation, one or more relaxing videos will be shown to help reduce stress and anxiety (up to 10 min). Finally, general psychoeducational information about the ICU environment and the characteristics of the cognitive, mental and physical status of patients with critical illness will also be provided (about 5 min). By default, this information will be provided only once on the first day that the patient does not present delirium (score ≤ 2 on the CAM-ICU-7) but will be repeated as many times as necessary in subsequent sessions if requested by the patient or family members. Due to changes in mental status and mobility level and medical complications that may arise during the ICU stay, the study staff administering and supervising the intervention will also be able to choose which specific cognitive and relaxation protocols and difficulty levels are administered in each session, always within the parameters of each patient’s profile. The patient’s needs and preferences (e.g., the best time in the morning to apply the intervention, the cognitive and relaxation protocols to be administered) will also be considered, if they are safe and compatible with the patient's profile.

Patients will be constantly monitored during the intervention as part of standard ICU care. This will provide information on changes in mental status, mobility level and physiological parameters (e.g., peripheral oxygen saturation [SpO2], respiratory rate [RR] and heart rate [HR]), allowing the study staff to adapt the interaction, workload and duration of each session to the type of patient profile in real time. Adverse events (e.g., unsafe physiological parameters, unintentional removal of catheters, endotracheal tubes or tracheostomy cannulas) and tolerability issues (e.g., fatigue, extreme sleepiness, confusion) during the intervention will result in interruption or early termination of the session. Interruption or early termination of a session will not preclude participation in subsequent sessions if safety criteria are met (see “Safety and tolerability data” and “Harms and adverse event reporting” for details).

The intervention will be discontinued if patients voluntarily withdraw consent or, if they have not yet been able to give consent themselves, their authorized representative voluntarily withdraws consent, requests to stop receiving the intervention, are transferred to another ICU or die during ICU stay. At the discretion of the clinical staff, the intervention will also be discontinued if there are changes in the patient's medical condition, such as worsening disease, that make continued participation inadvisable or if there are safety concerns that poses a risk to participants. In the event of discontinuation of the intervention, patients will continue to receive standard ICU care. Participants should not participate in other RCT intended to stimulate cognition and provide relaxation during or after the ICU stay.

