### Outcomes

The primary outcome is objective cognition 12 months after ICU discharge assessed with a global cognition index (z-score: mean = 0, standard deviation = 1) established on the basis of previous studies [6–8, 13, 14] and composed of validated neuropsychological measures of attention (Forward Digit Span subtest of the Wechsler Adult Intelligence Scale-IV, WAIS-IV), working memory (Backward Digit Span subtest of the WAIS-IV), learning/memory (Rey Auditory Verbal Learning Test, RAVLT), executive function (Trail Making Test, TMT; Stroop Color and Word Test, SCWT; FAS verbal phonemic fluency test) and processing speed (Digit Symbol-Coding subtest of the WAIS-IV; Symbol Digit Modalities Test, SDMT) [30–35].

The secondary outcome is the safety of the intervention assessed by considering the number of sessions terminated early due to unsafe events on physiological parameters [19].

Other outcomes are comfort experienced during ICU stay assessed at ICU discharge with the Patient Evaluation of Emotional Comfort Experienced questionnaire (PEECE) (range 0–48) [36], subjective cognition 12 months after ICU discharge assessed with the Perceived Deficits Questionaire-5 (PDQ-5) (range 0–20) [37, 38], anxiety 12 months after ICU discharge assessed with the Generalized Anxiety Disorder-7 questionnaire (GAD-7) (range 0–21) [39, 40], depression 12 months after ICU discharge assessed with the Patient Health Questionnaire-9 (PHQ-9) (range 0–27) [41, 42], PTSD 12 months after ICU discharge assessed with the Treatment-Outcome Post-Traumatic Stress Disorder Scale (TOP-8) (range 0–32) [43, 44], functionality 12 months after ICU discharge assessed with the World Health Organization Disability Assessment Schedule 2.0 (WHODAS 2.0) (range 0–100) [45], and HRQoL 12 months after ICU discharge assessed with the Short-Form Health Survey (SF-12) (range 0–100) [46, 47].

For all outcomes, except for intervention safety which is only evaluated in the RGS-ICU group, the difference between the RGS-ICU and TAU groups will be considered.

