#### Safety and tolerability data

The safety of the intervention will be assessed by considering the number of sessions terminated early due to unsafe events in physiological parameters, analyzing SpO2, RR and HR [19]. The safety analysis will be based on expert consensus criteria for unsafe active mobilization of patients with critical illness on MV: SpO2 < 90%, RR > 35 breaths/minute and HR > 150 beats/minute, all during ≥ 5 min [56]. Out-of-range values at the start of the session or changes > 20% from baseline in any physiological parameter will also be considered unsafe events requiring that the session not be started or terminated, respectively. Failure to start a session or early termination of a session will not preclude participation in subsequent sessions if the safety criteria are met. Safety physiological parameters will be automatically displayed on bedside monitors using advanced continuous monitoring systems as part of standard ICU care. An alarm will be triggered if an unsafe event occurs. Study staff guiding and supervising the sessions will also visually check the stability of physiological parameters to ensure the safety of the intervention and that no avoidable adverse events (e.g., unintentional removal of catheters, endotracheal tubs or tracheostomy cannulas) occur.

The tolerability of the intervention will be assessed by considering the number of completed sessions and the patients' tolerance to the interaction and workload of the cognitive and relaxation protocols. Therefore, the number of interruptions, the cause of the interruption (e.g., fatigue, extreme sleepiness, confusion), as well as the type and difficulty level of the cognitive and relaxation protocols in which the interruption occurred will be recorded.

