#### Additional variables

For each cognitive stimulation and relaxation session with the RGS-ICU platform, the start and end time, the protocols performed, the duration of each protocol, the difficulty levels performed (only cognitive protocols), the number of hits and failures per difficulty level (only cognitive protocols), and the number and reasons for interruption and/or early termination of the sessions (if applicable) will be recorded.

The following data will also be collected: days of delirium and invasive MV, days of ICU and hospital stay, discharge destination (home, home hospitalization or social-health center), days to return to work after ICU discharge (working age patients only), number of hospital and ICU readmissions, and need for psychopharmacological treatment, psychotherapy, cognitive rehabilitation and physical rehabilitation after ICU discharge.

These data will be collected at ICU discharge or during post-ICU follow-up visits, as appropriate. If necessary, electronic medical records will be reviewed (Table 4).

**Table 4 Tab4:** Additional variables collected during and after the ICU stay

	**Day** **1**	**Day** **2**	**Day** **…**	**Day 28/ICU discharge**	**3 months after ICU discharge**	**12 months after ICU discharge**
**Intervention characteristics (for each session)**^a^						
Star and end time	x	x	x	x		
Protocols performed	x	x	x	x		
Duration of each protocol	x	x	x	x		
Difficulty levels performed (only cognitive protocols)	x	x	x	x		
Number of hits and failures per difficulty level (only cognitive protocols)	x	x	x	x		
Number and reason for interruption or early termination (if applicable)	x	x	x	x		

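### An unsafe physiological event may lead to interruption in one section and requires termination in another, and the secondary safety outcome counts only terminations

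*Protocol article*

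**What the plan says.** Four parts of the protocol article bear on this.

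- **Experimental condition: RGS-ICU group.** The adverse events are introduced as "Adverse events (e.g., unsafe physiological parameters, unintentional removal of catheters, endotracheal tubes or tracheostomy cannulas". Together with tolerability issues such as fatigue, they "during the intervention will result in interruption or early termination of the session". The next sentence keeps the two responses as alternatives: "Interruption or early termination of a session will not preclude participation in subsequent sessions if safety criteria are met". It then refers the reader to the safety and harms sections for details.
- **Safety and tolerability data.** The safety analysis uses the limits "SpO2 < 90%, RR > 35 breaths/minute and HR > 150 beats/minute, all during ≥ 5 min". Out-of-range values at the start and "changes > 20% from baseline in any physiological parameter" are added, and these "will also be considered unsafe events requiring that the session not be started or terminated, respectively". Interruption is not offered here for an unsafe event. The number and cause of interruptions come in the following paragraph, as tolerability measures.
- **Outcomes.** The only secondary outcome is the "number of sessions terminated early due to unsafe events on physiological parameters". The sections on safety data and statistical methods use the same definition. It is evaluated in the RGS-ICU group only and analysed descriptively.
- **Additional variables.** For each session, "the number and reasons for interruption and/or early termination of the sessions (if applicable) will be recorded".

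**The concern.** The protocol gives the same kind of event two possible responses, depending on which section is read. The secondary outcome is defined by the response (early termination) and not by the event, so the conflict carries over into the outcome. If staff interrupt a session for an unsafe physiological event, which the intervention section allows, that session falls outside the safety count and into the tolerability count.

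The error can run in one direction only. Interruptions can lower the number of terminated sessions but cannot raise it, and a low number is what the secondary hypothesis of safety expects. No control arm would reveal a shortfall, because the outcome is measured in one group. Two hospitals could also classify the same event differently while each follows a section of the protocol.

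**Working it through.** The protocol gives no expected number or rate of unsafe sessions, so there is no stated figure to reproduce. The check compares the sections and then applies the outcome's own definition.

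**Step 1. Which response does each section allow?**

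| Event | Experimental condition section | Safety and tolerability data section |
|---|---|---|
| Out-of-range value at the start of a session | not addressed separately | session not started (explicit) |
| Change above 20% from baseline | interruption or early termination | termination (explicit) |
| Sustained SpO2, RR or HR limit crossed | interruption or early termination | termination (implied) |
| Fatigue, extreme sleepiness, confusion | interruption or early termination | interruptions recorded under tolerability |

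In the third row, termination is implied because the added criteria are said to count *also* as unsafe events with that consequence. The conflict is therefore explicit for changes above 20% and inferred for the sustained limits. It does not arise for values at the start, since a session that has not begun cannot be interrupted.

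**Step 2. Which count does each response enter?**

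- Terminated early for an unsafe physiological event: counted in the secondary outcome.
- Interrupted for an unsafe physiological event: not counted in the secondary outcome. It is recorded in the session log with its reason (Additional variables, Table 4), falls among the interruptions under tolerability, and is collected as an adverse event (Harms and adverse event reporting).
- Not started: not a session terminated early, so not counted, and no exposure took place.

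**Step 3. Size.** Let U be the number of started sessions with an unsafe physiological event, and q the share of these that are interrupted rather than terminated.

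- Sessions counted by the outcome = U × (1 − q).
- Relative shortfall = [U − U × (1 − q)] / U = q.

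The documents give neither U nor q. As an illustration with assumed values only:

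- q = 0: 1 − 0 = 100% of unsafe sessions counted.
- q = 0.25: 1 − 0.25 = 75% counted.
- q = 0.5: 1 − 0.5 = 50% counted.

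The value q = 0 applies if the safety section is always followed.

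**The case against.** The strongest reply is that the two sections can be read together. The intervention section summarises two kinds of event and two responses without saying that each response is open for each event. Its next sentence sends the reader to the safety section, which sorts them: unsafe events mean termination or no start, and interruptions belong to tolerability. The outcome matches that sorting. On this reading q is zero, and resuming after an unsafe event would be a protocol deviation, to be documented as such. This reading is available, but the text does not settle on it. Unsafe physiological parameters are the first example in the sentence that allows interruption, that sentence does not reserve interruption for tolerability issues, and the cross-reference is attached to the statement about later sessions.

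A reader might also infer that interrupted unsafe sessions would not be reported as safety information at all. The documents do not support this. The section on harms names unsafe physiological parameters among the adverse events to be collected and analysed for all participants, and the session log keeps the reason for every interruption. Only the entry in the secondary outcome is at risk.

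Three further limits stand. The protocol does not define interruption and does not mention resuming after an unsafe event, so pausing and resuming is an inference from the word being an alternative to early termination. Numerical limits, automatic alarms, harmonization workshops and a team of four trained investigators reduce the scope for differing practice. Finally, the outcome is descriptive, with no test or threshold that a small shortfall could tip.

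**Conclusion.** The point holds as an inconsistency between two sections that reaches the only secondary outcome. One section permits interruption after an unsafe physiological event, the other requires termination, and the outcome counts terminations alone. An unsafe session that is interrupted would be missing from the outcome, though not from the trial's data.

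The size of any undercount is unknown. It is zero if termination always follows an unsafe event, and otherwise equals the share of unsafe sessions that are interrupted. Its direction is known: it can only make the intervention look safer. It would be tempting to conclude that the safety result will be biased by some stated amount, but the documents give no event rate and no share of interruptions from which to derive one.

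The conclusion assumes that interruption means something other than early termination, as the protocol's wording suggests. Severity is minor to moderate: the conflict can be reconciled and the data are kept, but it affects a named outcome.

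**What to change.** 1. Reconcile the sections on the experimental condition and on safety and tolerability data, so that both state the same response to an unsafe physiological event during a session, including for the sustained SpO2, RR and HR limits. State what interruption means. Which response applies is a clinical decision, and this review does not propose one.
2. Independently of that decision, define the secondary outcome as the number and proportion of started sessions in which an unsafe physiological event occurred, whether the session was interrupted or terminated. Show early terminations as a subset, so that the count as now defined remains visible. List sessions not started because of out-of-range values separately. Use the same wording in the sections on outcomes, safety data and statistical methods.

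This definition holds under either handling rule. It needs no new data collection, because the number and reasons of interruptions and terminations are already recorded for each session. The cost is a change of wording and a descriptive safety figure that may look slightly less favourable.
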